### Data Analysis

Given that this is not a randomized trial, an intention to treat analysis is not essential. To maximize understanding of what works for whom, we seek to measure the intervention effect on those participants who actually receive the intervention—and we also seek to understand the factors that influence completion and non-completion of COS-P, as well as variations in response (71). Thus, data in this study will primarily be analyzed to measure the treatment effect on participants who received COS-P as intended. Complete Time 1 and Time 2 data for study participants who attend at least six of the eight COS-P sessions will be included in these analyses, together with data from clinical files and information collected during facilitator fidelity interviews, if appropriate. For participants who (a) attend 5 or fewer COS-P sessions and/or (b) do not complete Time 2 measures, treatment effect will not be measured; only Time 1 data, clinical file data and information collected during facilitator fidelity interviews will be analyzed, to explore whether characteristics of these caregivers distinguish them from completers and/or influence failure to complete the intervention.

Analyses will be conducted using SPSS Version 26 (72). Descriptive analyses will be used to profile and compare the characteristics of the treatment and waitlist control groups in the four participating sites. Bivariate correlations and independent samples *t-*tests will be used to explore relationships among the outcome variables and any potential covariates. As group allocation is not randomized, and recruitment is undertaken across four sites with different characteristics, the two groups may differ on distribution of demographic and risk factors which may impact on intervention effects. Baseline comparability will be assessed using independent samples *t*-tests (for continuous variables) and chi-square tests of independence (for categorical variables). Mixed design ANOVA will be used to control for any observed differences in baseline characteristics. Due to anticipated differences among participant cohorts from the four different sites, child age and depression symptoms (EPDS score at Time 1) will be included as *a priori* covariates. If sample size and composition allow, results will be stratified by site.

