## Methods and Analysis

### Design

This study is a multi-site non-randomized controlled effectiveness study of COS-P, with treatment and waitlist control group participants undergoing assessment at two time points. The multi-site design both reflects the broad dissemination of COS-P and enables recruitment of sufficient participants to meet sample size requirements (see power analysis, below). The study design was determined in consultation with the study sites (see study setting, below); senior managerial staff indicated willingness to support incorporation of the study into their service, but maintained that they could not accommodate a randomized trial. Thus, participant allocation to treatment and waitlist control conditions will not be randomized, but dependent on the scheduled timing of the COS-P group in which they are enrolled. At study entry, participants whose COS-P group will commence within 7 weeks will be allocated to the treatment group. Participants whose COS-P group will commence eight or more weeks hence will be offered a place in the waitlist control group. Circumstances that may contribute to the latter include a long COS-P waiting list at the study site, registering just after a COS-P group has been filled or has started, inability to attend the next available group due to scheduling clashes, being assigned to a group that is subsequently canceled due to insufficient numbers, and the long gap between groups over the summer shutdown period. However, both treatment and control group participants must be determined to be “COS-P-ready” according to standard clinical procedure prior to their participation in the study. Waitlist control group participants will be free to engage with other forms of treatment or support within and outside of the organization prior to commencing the group. This study has been approved by the relevant university, health department and service-specific ethics committees (Macquarie University Human Research Ethics Committee: 5201600788; St John of God Healthcare Human Research Ethics Committee: 1153; Sydney Local Health District Ethics Review Committee: HREC/17/RPAH/285 & SSA/17/RPAH/432; ACT Health Human Research Ethics Committee: ETH.9.17.221E).

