### Study Setting

The study will be undertaken in collaboration with four community child and family health organizations (study sites) in two Australian cities located in separate states/territories. There are two study sites in each city. Three of these organizations have an explicit focus on perinatal mood problems, all offer COS-P in their suite of services for families with young children (aged 0-5) and all expressed an interest in participating in a collaborative evaluation study. See Table 1 for site details. All study sites routinely deliver COS-P groups, generally four times per year during school terms. All sites offer COS-P to current clients, and two also make the program available to parents from the community. One site delivers COS-P to clients only toward the end of other treatment, whereas the other three do not specify timing for the intervention. In all cases, group facilitators use their clinical judgement to assess suitability for the group, based on prior casework and/or a pre-group interview (face-to-face or by phone).

**Table 1 T1:** Overview of study sites.

	**Site 1 Tresillian Family Care Centres**	**Site 2 Raphael Services NSW St John of God Healthcare Social Outreach**	**Site 3 ACT Health Perinatal and Infant Mental Health Consultation Service**	**Site 4 Marymead Centre for Early Life Matters**
Type of service	Early parenting support	Perinatal and infant mental health	Perinatal mental health	Early parenting support
Referral pathway/s	•Health professionals •Self-referral for groups	•General practitioners and medical specialists	•Health professionals	•Health professionals •Education professionals •Self-referral
Accessed by parents with…	Parenting challenges, often around feeding, sleeping, settling, adjustment & associated perinatal mental health issues	Mental illness in the perinatal period (pre-conception to index child age 4)	Perinatal mood disorders (pregnancy to 12 months post-partum)	Concerns about parenting, adjustment, mental health, or child relationship, emotional, or behavioral issues
Child age range	0–5 years	Pre-conception to 4 years old	0–5 years	0–8 years
Professional staff	•Nurses •Social Workers •Psychologists •Psychiatrists/Registrars •Pediatricians •GPs	•Psychiatrists/registrars •Clinical Psychologists •Social Worker •Mental Health Nurses	•Medical Officer •Psychiatrists/Registrars •Psychologists •Social Workers •Occupational Therapists •Nurses	•Psychologists •Social Workers •Counselors

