### Participants

Eligible participants will be primary caregivers and/or their partners, with a child aged 0–60 months (at study entry), who are registered to attend a COS-P group at one of the study sites during the 18–24 month study period. Study exclusion criteria (an acute disorder or one likely to limit participation; insufficient English proficiency to complete study measures) are, in fact, also site exclusion criteria for referral to COS-P groups. They are routinely assessed at the time of engagement with the organization and also during routine pre-group-enrolment screening. Any participant whose assessment indicates risk to parent or infant will be triaged into other appropriate treatments. Thus, the single study-specific exclusion criterion is having attended COS-P sessions prior to study enrolment. Participants will receive no reimbursement for study participation.

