### Intervention

At all study sites, COS-P will be facilitated to groups of parents according to the original program manual (6) utilizing the associated DVD, over 8 weekly 90 to 120-min sessions; one manual chapter (with associated DVD content) to be completed *per session*. Following standard COS-P research practice, intervention completion will be defined as attendance at a minimum of six sessions ([name] MD, Research Liaison and Medical Director—Circle of Security International, personal communication, 15 August 2017).

To maximize intervention fidelity, collaborating study sites have been chosen, in part, for their adherence to the COS-P manual in their routine delivery of COS-P. Beyond this, as the study aims to evaluate COS-P-as-delivered, intervention fidelity will be assessed by the research team, through post-group interviews with each COS-P facilitator (see interview details below).

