#### Monitoring Intervention Fidelity

##### COS-P fidelity interview

A brief structured interview was developed to track program fidelity during this study. Questions administered to all COS-P facilitators at the end of each group will probe adherence to the COS-P manual and DVD clips. Any content excluded or added will be noted. This interview will also provide an opportunity for facilitators to share any factors they noted during the group that might influence intervention completion or outcomes for specific participants, e.g., divorce, separation, or death of a significant other during the course of the group, presence of a partner in the group, etc.

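### Participants share COS-P groups, and sometimes households, but are analysed and counted as independent; standard errors are probably somewhat too small, mainly for the questionnaire outcomes

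*Protocol article*

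**What the plan says.** Four parts of the protocol article bear on this.

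- **Delivery and allocation.** Under Intervention, "COS-P will be facilitated to groups of parents according to the original program manual". Under Design, allocation is "dependent on the scheduled timing of the COS-P group in which they are enrolled". Waitlist participants complete both assessments before they start COS-P (Procedure). Under Study Setting, "All study sites routinely deliver COS-P groups, generally four times per year during school terms".
- **Couples.** Under Participants, "Eligible participants will be primary caregivers and/or their partners". The section on the COS-P fidelity interview lists "presence of a partner in the group" among the things facilitators may report.
- **Analysis.** Under Data Analysis, "Mixed design ANOVA will be used to control for any observed differences in baseline characteristics". The other tests named are independent samples t-tests, chi-square tests and bivariate correlations, in SPSS. On covariates, "child age and depression symptoms (EPDS score at Time 1) will be included as" a priori covariates. Stratification by site is conditional on numbers.
- **Sample size.** The Sample Size Calculation section asks for 128 participants for the questionnaires, raised to 154 for attrition, and 40 raised to 48 for the interview and observational subsample.

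The article mentions no COS-P group term, couple term, ICC, robust standard error or design effect.

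**The concern.** Treated participants in one COS-P group share facilitators, peers and any departure from the manual over eight weeks. Their changes from Time 1 to Time 2 may therefore resemble each other. Waitlist participants do not meet as a COS-P group during their assessment window, so this dependence arises in one arm only (a partially nested design). Two partners may also report on the same child.

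A mixed design ANOVA has one between-person factor (arm) and one within-person factor (time). It handles the correlation between a person's two scores but has no place for correlation between people. Despite the similar name, it is not a mixed-effects model. Stratifying by site does not remove group or couple correlation either.

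At stake is the precision of the main comparison. With positive correlation, intervals are too narrow and tests reject too often. The 0.005 level, set for multiple comparisons, is affected proportionately more than a 0.05 level.

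**Working it through.** **The plan's own figure.** A two-sample t-test with a standardised difference of 0.5, two-sided 5% level and 1:1 allocation needs 64 per arm, 128 in total (power 80.1%). At the stated 0.005 level the same test needs 218. A repeated-measures between-person test (f = 0.25, level 0.005, 80% power) needs 112 at a Time 1-Time 2 correlation of 0 and 132 at 0.2, so 128 could also come from there. The article does not say which calculation was used, and that is a separate matter. Each of these calculations counts independent individuals, and the article mentions no clustering allowance.

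**Treated participants per group** (1:1 allocation is assumed; no ratio is stated)

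- Groups: 4 sites x 4 per year x 1.5 to 2 years = 24 to 32.
- Treated, at recruitment: 154/2 = 77, so 77/32 = 2.4 to 77/24 = 3.2 per group.
- Treated, at the analysed size: 128/2 = 64, so 64/32 = 2.0 to 64/24 = 2.7 per group.
- Treated, in the subsample: 48/2 = 24, so 24/32 = 0.75 to 24/24 = 1.0 per group.

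These figures assume even spread over all groups. An average of 8 per group would put all 77 treated participants into about 10 groups (77/8 = 9.6).

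**Effect of group clustering.** With m treated participants per group and ICC the correlation of *change* within a group:

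- design effect in the treatment arm: DE = 1 + (m - 1) x ICC
- variance ratio for the difference between arms: (DE + 1)/2
- actual two-sided error: 2 x [1 - Phi(z / sqrt(variance ratio))], with z = 1.960 at 5% and 2.807 at 0.5%

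The ICC values are assumptions.

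| m | ICC | DE | Variance ratio | SE ratio | Nominal 5% | Nominal 0.5% | 128 becomes |
|---|---|---|---|---|---|---|---|
| 2 | 0.05 | 1.05 | 1.025 | 1.012 | 5.3% | 0.56% | 132 |
| 2 | 0.10 | 1.10 | 1.05 | 1.025 | 5.6% | 0.62% | 135 |
| 3 | 0.05 | 1.10 | 1.05 | 1.025 | 5.6% | 0.62% | 135 |
| 3 | 0.10 | 1.20 | 1.10 | 1.049 | 6.2% | 0.74% | 141 |
| 8 | 0.05 | 1.35 | 1.175 | 1.084 | 7.1% | 0.96% | 151 |
| 8 | 0.10 | 1.70 | 1.35 | 1.162 | 9.2% | 1.57% | 173 |

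In the subsample, m is about 1, so DE is about 1 and the effect is close to nil.

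**Effect of couples, taken alone.** Let q be the share of participants enrolled as couples and r the within-couple correlation. Both partners in the same arm: variance ratio 1 + q x r. Partners in opposite arms: 1 - q x r. For q from 0.1 to 0.4 and r from 0.2 to 0.5 (assumed), the SE ratio is 1.01 to 1.10 in the first case and 0.99 to 0.89 in the second. Allocation follows the timing of the group, so partners registering together would usually share an arm, but the article does not say so.

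**The case against.** The strongest reply is that the effect is small. The plan's own schedule implies only two or three treated participants per group, and stable differences between groups cancel in a comparison of change. This stands, and it is why the main range uses 2-3 per group and an ICC for change. Larger clusters cannot be excluded, because the Discussion expects unequal numbers across sites.

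A second reply is that a condensed article leaves variance structure to a fuller plan. This has less force here. The article names the model, the tests, the covariates and the software, and that model cannot hold the dependence.

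A third is that partner presence is not overlooked. Facilitators can report it, and fidelity-interview information may enter the effect analyses if appropriate. That is true, but it is not an adjustment for correlated outcomes.

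A reader might also draw three stronger conclusions that the documents do not support:

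- **That every outcome is affected.** The interview and observational measures come from the 48-person subsample, with about one treated participant per group if evenly spread.
- **That a 5% test in fact runs near 9%.** This needs both about 8 treated participants per group and an ICC of 0.10.
- **That the authors recognised clustering and then ignored it.** The Real World Research section calls trials of group interventions more complex because of scheduling and minimum numbers, which is logistics and not correlated outcomes.

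**Conclusion.** The point holds in a limited form. The article fixes an analysis and a sample size that treat participants as independent, although the design puts treated participants in shared groups and allows couples.

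That the standard errors are too small is conditional, not established. It requires positive correlation of change within COS-P groups, or within couples in the same arm. This is the usual expectation, but the documents give no figure for it, and couples split across arms would push the other way.

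Under the stated assumptions the error is modest: a few tenths of a percentage point to just over one point on a 5% test. It becomes material only if enrolment is concentrated in few groups. It concerns mainly the questionnaire outcomes. The analysis should be changed, but this alone does not undermine the study.

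**What to change.** 1. For the questionnaire outcomes, replace the mixed design ANOVA with a linear mixed model of the Time 2 score, adjusted for the Time 1 score, child age and Time 1 EPDS, or a corresponding model of the change score. Name one in advance, because the two can differ when arms are not randomised.
2. Include a COS-P group random effect in the treatment arm only, with Satterthwaite degrees of freedom. Modelling the Time 2 score or the change matters: a group intercept simply added to a two-time-point model would not capture clustering in change, which is the treatment effect here.
3. Handle couples with a household random effect. If it cannot be estimated, run a sensitivity analysis that keeps one caregiver per child.
4. Record group and household identifiers under the study ID.
5. State beside the power figure that it assumes independence, and give a design-effect range such as the one above.

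The cost is slightly wider intervals and one extra linking variable. The household link is a new step, because clinical file data reach the research team by client study ID only. With such small groups and probably few couples, a variance component may be estimated at zero or a fit may fail, so a fallback should be written down in advance. Recruitment and assessments are unchanged.

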## Discussion

Widely disseminated yet strikingly under-researched, COS-P is a program with evident appeal and potential, but little evidence of effectiveness. This study is designed to help address this evidence gap. It is the first COS-P effectiveness study in Australia, one of the first worldwide, and one of the few to utilize a control condition. The collaboration of four clinical services currently offering COS-P to clients provides a valuable opportunity to measure program effectiveness in these real-world settings.

Given the complexity of the study context, several challenges are expected, which will need to be managed at different stages of the study. Firstly, there is increased potential for baseline differences among treatment and control group participants due to the non-randomized design. Although it cannot match the rigor of an RCT, the repeated measures design enables investigation of potential differences between groups in preliminary analyses, so the influence of any known differences can be controlled in main analyses, reducing potential confounds. However, we acknowledge the possibility of unknown confounding variables. Secondly, the differences between study sites with respect to client numbers, characteristics, referral pathways, treatment protocols (outside of COS-P), and child age, may increase sample heterogeneity and may affect generalization of findings. If sample size allows, results will be stratified by site, but we acknowledge that this may not be possible. In addition, staff turnover, clinical loads, and/or lack of clinician buy-in to the study may reduce research capacity in some sites at some stages of the study. Inherent site differences and staffing challenges may lead to unequal participant numbers across the four sites, complicating data analysis. Finally, we acknowledge it is possible that elements of the Circle of Security model are diffused throughout the study sites, informing broader practice, which may compromise a clear distinction between the COS-P treatment and any TAU provided to the waitlist control group. These challenges will be carefully documented and considered in study analyses and interpretation and discussion of results.

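### Confounding is only partly controlled: site is not a model term, and covariates beyond child age and Time 1 EPDS depend on an observed baseline difference

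*Protocol article*

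**What the plan says.** Under Design, "participant allocation to treatment and waitlist control conditions will not be randomized, but dependent on the scheduled timing of the COS-P group" in which the participant is enrolled: a start within 7 weeks means treatment, 8 or more weeks means waitlist. Several reasons for a long wait are listed, and one is expressly tied to the site: "Circumstances that may contribute to the latter include a long COS-P waiting list at the study site". Waitlisted participants may use other support in the meantime.

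The sites are described as unlike one another. The Discussion names "differences between study sites with respect to client numbers, characteristics, referral pathways, treatment protocols (outside of COS-P), and child age", and Study Setting adds: "One site delivers COS-P to clients only toward the end of other treatment, whereas the other three do not specify timing".

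Data Analysis then fixes the adjustment in three parts:

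- Two covariates are set in advance, on account of site: "Due to anticipated differences among participant cohorts from the four different sites, child age and depression symptoms (EPDS score at Time 1) will be included".
- Baseline comparability is checked with t-tests and chi-square tests, and a mixed design ANOVA "will be used to control for any observed differences in baseline characteristics".
- Site itself appears only here: "If sample size and composition allow, results will be stratified by site". The Discussion concedes that this may not be possible.

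**The concern.** In a non-randomised comparison the adjustment set is the main defence against bias. The article connects site to the waiting time that determines arm, and to client type and concurrent treatment, which may affect how much a caregiver changes over the 7 to 11 weeks. That makes site a plausible common cause of arm and outcome. Child age and EPDS capture part of what differs between sites. They cannot stand in for referral route, concurrent treatment or stage of treatment.

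Two features of the rule are weak. First, stratifying results needs numbers in every site-by-arm cell, whereas adjusting for site does not, so a sample-size condition is no reason to leave site out of the model. Second, a non-significant baseline test does not show balance. At these sample sizes it mainly shows that the test had little power, and a real imbalance then goes unadjusted.

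**Working it through.** **Inputs.** From Sample Size Calculation: 128 analysed for questionnaires and 40 for interview and observation. From Study Setting: 4 sites. Assumed, because not stated: equal arms, two-sided 0.05 for the baseline tests, and a medium effect of d = 0.5. The article gives no figure for confounding, so there is none to reproduce; 128 and 40 serve only as analysis sizes.

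**1. Power of the baseline screen.** Two-sample t-test, noncentrality = imbalance × √(n₁n₂/(n₁+n₂)). For 0.3 SD with 64 per arm this is 0.3 × √32 = 1.70.

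| True imbalance | 64 v 64 | 20 v 20 |
|---|---|---|
| 0.2 SD | 20% | 10% |
| 0.3 SD | 39% | 15% |
| 0.4 SD | 61% | 23% |
| 0.5 SD | 80% | 34% |

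A 0.3 SD imbalance is thus missed about 61% of the time in the questionnaire sample and 85% in the subsample.

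**2. What can bias the contrast.** The outcome is measured twice, so a constant site difference in level cancels in group-by-time. What remains is: difference in natural change × difference in site share between arms. With assumed inputs, 0.3 × 0.20 = 0.06 SD and 0.5 × 0.30 = 0.15 SD.

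**3. Simulation (assumed inputs).** N = 128, 4 equal sites, no true effect, 4000 runs. Sites with a higher share treated were also given the larger natural change, which is an unfavourable alignment. Child age and EPDS were not modelled.

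| Shares treated across sites | Site mean change | Bias without site | Type I error without site | Site-by-arm chi-square significant |
|---|---|---|---|---|
| 40 to 60% | ±0.25 / ±0.5 SD | 0.06 / 0.11 SD | 6% / 9% | about 29% |
| 30 to 70% | ±0.25 / ±0.5 SD | 0.12 / 0.23 SD | 10% / 24% | about 88% |
| 20 to 80% | ±0.25 / ±0.5 SD | 0.17 / 0.33 SD | 15% / 41% | nearly 100% |

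Hand check for 30/40/60/70% and ±0.25 SD: [(0.2 × 0.25 + 0.1 × 0.083) × 2/4] / 0.25 = 0.117 SD. With site in the model, bias was about 0 and type I error about 5% throughout.

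**4. Cost of adjusting for site.**

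- Four sites use 3 degrees of freedom. For a plain two-sample comparison at N = 128, power moves from 80.15% to 80.13% at alpha 0.05, and from 49.1% to 49.0% at 0.005. Only the change matters here, not how 128 was derived.
- Collinearity: with shares of 30/40/60/70%, the mean of p(1−p) is (0.21 + 0.24 + 0.24 + 0.21)/4 = 0.225, a variance factor of 0.25/0.225 = 1.11.
- In the subsample, with k covariate terms unrelated to arm, expected variance inflation is (n−3)/(n−k−3). Two covariates as planned: 37/35 = 1.06. Site plus those two (k = 5): 37/32 = 1.16. Site plus six covariates (k = 9): 37/28 = 1.32.
- Stratification by contrast leaves 128/(4 × 2) = 16 per arm per site, even if numbers are equal.

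**The case against.** A reader might infer that confounding is left uncontrolled. The text does not support that. Two covariates are fixed in advance, chosen because of site differences; observed differences on other characteristics are also to be controlled; the pre-post contrast removes stable level differences; and the Discussion acknowledges unknown confounders.

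A reader might also infer that site determines waiting time. Design lists five circumstances, of which only the long waiting list is expressly tied to the site, and Study Setting says groups generally run four times a year at all sites. Site as a common cause is plausible but not demonstrated.

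Nor does the article say that covariates will be chosen by their correlation with outcomes. It says these relationships will be explored; the stated rule concerns baseline differences only.

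If site were among the categorical variables tested, the article's own rule would usually catch the worst imbalances (about 88% of runs at shares of 30 to 70%). The text does not say that site is tested, and at 40 to 60% the test would catch only about 29%. Setting 0.15 SD against a 0.5 SD effect and calling it a 30% distortion would take both assumed inputs at their maximum and credit nothing to child age and EPDS.

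A condensed article may leave coding details to a fuller plan. Here, however, it states the adjustment rule itself, and the point concerns that rule. The objection that a long covariate list is costly at n = 40 stands, and it limits the remedy.

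**Conclusion.** The point holds in limited form. Confounding is partly controlled: child age and Time 1 EPDS are fixed, but site enters only as optional stratified results, and other confounders enter only on an observed baseline difference. That screen misses most imbalances of 0.2 to 0.3 SD at 64 per arm and most up to 0.5 SD at 20 per arm, assuming two-sided 0.05.

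The bias from omitting site acts through differences in change and cannot be sized from the article. The 0.06 to 0.15 SD range is an illustration that rests on assumed differences in natural change and site mix, and the simulation shows larger or smaller values under other assumptions. What is firm is that adjusting for site is cheap at N = 128, so the sample-size condition does not justify its absence from the model.

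**What to change.** - Include site as a fixed factor, with its interaction with time, in the main questionnaire models, whatever the baseline tests show. The interaction is needed because a site main effect alone removes only level differences, which already cancel. Keep stratified results as a supplement.
- Replace the significance screen with a short confounder set fixed in advance, added to child age and Time 1 EPDS. Candidates are variables the study names: current medication for a mental health disorder (listed under Procedure), and education, gender and language background (named as possible moderators in The Current Study) where they are collected.
- Report baseline balance as standardised differences.
- In the interview and observation subsample of about 40, limit adjustment to site, child age and Time 1 EPDS.

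The cost is a change of analysis wording, 3 degrees of freedom for site, a modest collinearity loss if arm shares differ by site, and a larger proportional loss in the subsample. A site that contributes only one arm would add nothing to the within-site contrast, and this should be reported if it occurs.
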